### Prevalence and severity of hypoxemia in children

Hypoxemia is defined as hemoglobin oxygen saturation below 90% at sea level, as measured by pulse oximeter (PO), pulse oxygen saturation (SpO2), or blood gas tests (arterial oxygen saturation, SaO2) [4]. Hypoxemia is a common sign of severity in acute respiratory and non-respiratory illness and greatly increases the risk of death [5–7]. According to setting and the severity of disease, it is estimated that at least 2% [8] to 80% [6, 9, 10] of children with serious illnesses including pneumonia have hypoxemia. Outpatient children and those with a clinical diagnosis of acute upper respiratory tract infection were at low risk of hypoxemia (pooled estimate 6 to 9%) [11]. Prevalence increased to 31 and 43% in emergency department patients and clinical pneumonia cases, respectively, and was even higher in hospitalized children (47%) and those with confirmed pneumonia by X-ray (72%). Hypoxemia also occurs in children with serious illness, such as sepsis, meningitis, neonatal infections, anemia, … [8].

In 12 secondary level hospitals in Nigeria, a prospective cohort study was setup among neonates (0–28 days of life) and children (1 month-14 years old) to report the prevalence of hypoxemia, the oxygen utilization and clinical predictors of hypoxemia measured at the hospital entrance [6]. Among the 23,926 participants enrolled, the prevalence of hypoxemia was 22.2% (95% CI: 21.2–23.2) in neonates, and 10.2% (95% CI: 9.7–10.8) in children. It was common in children with acute lower respiratory tract infection (28%), asthma (20%), meningitis (17%), malnutrition (16%), acute febrile encephalopathy (15%), sepsis (9%) and malaria (9%) and in neonates with neonatal encephalopathy (33%), prematurity (27%) and sepsis (21%). In this study, hypoxemia increased the adjusted risk of death by 6-fold in neonates and 7-fold in children [6].

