##### End of search

All enrolled children, classified as severe cases will be followed up to 14 days after inclusion. The official end of the research, except in the case of premature termination, is defined as the last day of follow-up Day-14 of the last child included in the study.

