#### Outcomes evaluation

Cross-sectional study of pathways and patterns of care will be conducted among all IMCI children eligible for PO use with caregiver consent by research PHC. Children will be recruited consecutively during the 12-month.

Direct and indirect costs will be collected for a representative sub-sample of two categories of children: IMCI outpatients (green and yellow cases) and severe cases requiring hospital transfer (5 per category per PHC per month, i.e. 1920 children in total).

Day-14 health outcome will be collected only for severe cases. To assess the child mortality on Day-14 of all severe cases identified with an accuracy of plus or minus 3% per country and adding 10% lost to follow-up, we aimed to recruit at least 710 severe cases aged 2 to 23 months (mortality estimated at 10%) and 375 children aged between 24 and 59 months (mortality estimated at 5%), i.e. 1085 children between 2 and 59 months old per country over 12 months, for a total of 4340 children. We will only describe mortality in neonates (aged less than 59 days) enrolling them all over the 12 months of the operational study with a maximum of 400 per country. Overall, we will follow a maximum of 1485 children per country, i.e. a maximum of 5940 severe cases over the study period, representing approximately 15% of the total IMCI population which will be a total of 40,000 children expected for the four countries.

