##### Analysis of associated factors to the main criteria

Factors associated with being a severe case (using paper or e-IMCI and using PO or not) among IMCI outpatients, being hospitalized among severe cases, non-referral among severe cases will be studied using a multivariate logistic regression, adjusting for clustered variables (PHC, support of IMCI paper or electronic, rural/urban location), and for individual data (age, sex, socio-demographics, IMCI classification illness, comorbidities, seasonality, distance from home to PHC or district hospital, SpO2 level threshold using PO,...), using robust standard error to take into account the cluster effect within each PHC. All *P* values will be two-sided, with P values < 0.05 considered statistically significant.Kaplan-Meier estimates of the cumulative probability of oxygen therapy delivery and Day-14 survival will be performed for all identified severe cases with hypoxemia, whether hospitalized or not. Day-14 mortality associated factors will be analyzed using logistic regression. Additionally, in a sensitivity analysis missing data will be handled by using a complete data analysis and will consider the maximum bias hypothesis replacing missing data or dropouts by death values.The pathways (hospital transfer) and patterns of care (access to oxygen therapy, volume, duration) will be analyzed and their correlates investigated using a logistic regression.

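### Kaplan-Meier for oxygen delivery, with untreated deaths censored, can overstate the share of hypoxemic children treated; oxygen volume and duration are also placed under logistic regression

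*Protocol article*

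**What the plan says.** The section on analysis of associated factors to the main criteria gives one method for two time-to-event quantities: "Kaplan-Meier estimates of the cumulative probability of oxygen therapy delivery and Day-14 survival will be performed for all identified severe cases with hypoxemia". The population is explicitly broad, "whether hospitalized or not". The section names no competing event, no cumulative incidence function and no rule for children who die without oxygen. Its one provision that involves death is a sensitivity analysis in which missing data or dropouts are counted as deaths; that concerns the outcome and leaves the oxygen curve as it is.

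The follow-up window comes from the section on the end of the research: "All enrolled children, classified as severe cases will be followed up to 14 days after inclusion".

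The same analysis section then says that the "patterns of care (access to oxygen therapy, volume, duration) will be analyzed and their correlates investigated using a logistic regression". It states no cut-point for volume or duration. The descriptive analysis section, by contrast, reports oxygen coverage as a percentage and summarises volumes and mean durations as quantities.

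**The concern.** A child who dies without oxygen can no longer receive it. If that child is censored at death, Kaplan-Meier treats the child as having the same chance of later oxygen as those still alive and untreated. One minus Kaplan-Meier then describes oxygen access in a hypothetical setting without death, not the share of children who were treated.

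The setting makes this more than a formality. The Discussion says that oxygen is lacking at primary health centers, and Table 2 schedules oxygen data only at hospital entry and discharge, so delivery largely waits for transfer. The denominator deliberately includes children who are never admitted. Planned Day-14 mortality in all severe cases is 10% (2 to 23 months) and 5% (24 to 59 months), and the curve is restricted to the hypoxemic subset. The Background cites a hospital cohort in which "hypoxemia increased the adjusted risk of death by 6-fold in neonates and 7-fold in children". Oxygen after a hypoxemia diagnosis is the step that connects pulse oximetry to benefit, so an error in one direction in this figure matters to readers making policy.

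The logistic-regression wording is a separate mismatch. Of access, volume and duration, only access is binary. The other two could be fitted only after a dichotomy that the text does not give and that could be chosen after the data are seen.

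**Working it through.** **Figure to reproduce.** None. The document gives no oxygen coverage, no time to oxygen and no share dying before oxygen. All inputs below except the 14-day window are assumptions, shown over a range.

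Notation: co is the true proportion receiving oxygen by Day 14, and cd is the proportion dying before oxygen. Follow-up is taken as complete.

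**1. Direction and bounds from timing alone.** Take 1,000 children, 500 receiving oxygen and 100 dying without it (true share 50.0%).
- All deliveries before the deaths: 500/1,000 = 50.0%, bias 0.
- All deaths before the deliveries: 500/900 = 55.6%, bias +5.6 points.
- Three successive intervals with (oxygen, death) of (250, 50), (150, 30) and (100, 20), oxygen counted first in each: the risk sets are 1,000, 700 and 520, so one minus Kaplan-Meier = 1 − (750/1,000)(550/700)(420/520) = 52.4%, bias +2.4 points.
- The same data with deaths kept in the risk set to Day 14, or with a competing-risk estimator: 50.0%.

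Removing deaths can only shrink the risk set at later deliveries, so the bias is never negative. It is zero when no untreated death precedes a delivery.

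**2. Slow access: constant hazards over 14 days.** Total cumulative hazard = −ln(1 − co − cd); oxygen part = total × co/(co + cd); one minus Kaplan-Meier = 1 − exp(−oxygen part). For co = 60% and cd = 10%: total = −ln(0.30) = 1.204; oxygen part = 1.204 × 0.60/0.70 = 1.032; result = 1 − exp(−1.032) = 64.4%.

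| True oxygen | Dying untreated | 1 − Kaplan-Meier | Excess (points) |
|---|---|---|---|
| 40% | 5% / 10% / 20% | 41.2% / 42.6% / 45.7% | 1.2 / 2.6 / 5.7 |
| 60% | 5% / 10% / 20% | 62.1% / 64.4% / 70.1% | 2.1 / 4.4 / 10.1 |
| 80% | 5% / 10% / 15% | 83.2% / 87.1% / 92.0% | 3.2 / 7.1 / 12.0 |

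Constant hazards spread deliveries over the whole fortnight. An oxygen hazard of 0.10 per day, for example, means a median time to oxygen of ln 2/0.10 = 6.9 days; 0.05 per day means 13.9 days.

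**3. Early access.** Let time to oxygen among recipients be exponential with mean 6, 12 or 24 hours, and time to untreated death exponential with mean parameter 3 or 7 days, both truncated at Day 14. Take co = 50% or 70% and cd = 5% or 10%, which makes 24 combinations. With Fo and Fd the two cumulative incidences, one minus Kaplan-Meier = 1 − exp(−∫ dFo/(1 − Fo − Fd)).
- Smallest excess: co 50%, 6 hours, cd 5%, 7 days gives 50.1%, +0.1 points.
- Largest excess: co 70%, 24 hours, cd 10%, 3 days gives 73.1%, +3.1 points.
- 23 of the 24 combinations are below 2 points.

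**4. Volume and duration.** No arithmetic applies. The descriptive analysis section treats both as quantities; the associated-factors section gives them a model for a binary outcome. The cost analysis section uses a mixed linear model for costs, so elsewhere the protocol does match a continuous outcome to a suitable model.

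**The case against.** The strongest reply is that the article names Kaplan-Meier without saying that deaths are censored. Event and censoring rules are often left to a fuller document, and if untreated deaths stayed at risk to Day 14 the curve would equal the crude proportion. That is true, but censoring at death is what a time-to-oxygen Kaplan-Meier does by default, and the text fixes the method without any qualification.

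A second reply is that severe cases are to be referred urgently, so oxygen is likely to come early or never, and the excess is then small. This stands, and it limits the size of the point.

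A third is that crude coverage, hospitalization rates, missed referrals and Day-14 deaths are also reported. This softens the harm. It does not correct the curve, which is the oxygen analysis explicitly covering hypoxemic children both in and out of hospital and may disagree with the percentage beside it.

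On logistic regression, one sentence covers several outcomes and may be compressed. The literal assignment still needs correcting, although the choice among continuous models is open.

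A reader might infer more than the document supports:
- That the curve always exceeds the true share. It does not when deliveries precede the untreated deaths.
- That an excess of several points is established. This requires slow access, and the largest values also need untreated deaths above the 5% to 10% planned as total mortality. The cited 6- to 7-fold risk gives no rate of death before oxygen.
- That the bias differs by country or by hospitalization. The document gives no mortality by either and plans no oxygen curves split by hospitalization. Children not admitted would have almost no oxygen events.

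**Conclusion.** The point holds for the named method. With censoring at death, one minus Kaplan-Meier for oxygen delivery is at or above the true proportion treated, and strictly above it when an untreated death precedes a later delivery. The direction is certain under that censoring; the size is not derivable from the document. Under the assumed inputs it is about 0 to 3 points if oxygen follows within about a day, and reaches roughly 10 points or more only if access is slow and untreated deaths are frequent. The Day-14 survival curve named in the same sentence is unaffected.

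The second part also holds: volume and duration are quantities, and logistic regression does not fit them without a cut-point that is not given.

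This affects a descriptive result in a non-comparative study. It has no consequence for design or sample size, but it is worth correcting because the error runs one way, bears on a policy-relevant figure, and costs little to remove.

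**What to change.** - Estimate oxygen delivery among hypoxemic severe cases by the cumulative incidence function (Aalen-Johansen), with death before oxygen as a competing event. Showing the curve for death before oxygen beside it would make untreated deaths visible.
- Keep Kaplan-Meier for Day-14 survival.
- Restrict logistic regression to receipt of oxygen (yes/no). Analyse volume and duration among recipients with a model suited to skewed continuous data, for example linear on the log scale or gamma, with standard errors clustered on primary health center, in line with the robust errors planned elsewhere in that section.

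The cost is analysis wording; no change in design or recruitment is needed. The one downside is that the reported oxygen-access figure may be slightly lower.

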##### Cost analysis will describe and analyze

The median overall direct cost of care per child managed (outpatients visits, hospitalization days, drugs, and oxygen, others, …) will be estimated (in USD) in each country according to the different categories of patients (non-severe cases, severe cases not transferred, and severe cases hospitalized). Within each category, we will investigate the effect of the support of IMCI used (paper or electronic) and PO use leading to IMCI reclassification. Indirect costs will be similarly estimated for the severe and non-severe cases.We will compare costs for managing non-severe cases, severe cases not transferred, and severe cases hospitalized using a mixed linear regression model.The PO implementation cost will be assessed exploring the additional cost of PO use for the health system and the remaining costs for households according to the severity of cases, the pathway of care and the patterns of care and will be studied in the 4 countries of the project.

### Ethics and consent to participate

The AIRE research protocol, the information notice (translated in vernacular languages), the written consent form and any other relevant document have been submitted to each national ethics committee, to the Inserm Institutional Evaluation Ethics Committee (IEEC) and to the WHO Ethics Review Committee (WHO-ERC). All the aforementioned ethical committees reviewed and approved the protocol and other key documents (Comité d’Ethique pour la Recherche en Santé (CERS), Burkina Faso n°2020–4-070; Comité National d’Ethique pour la Recherche en Santé (CNERS), Guinea n°169/CNERS/21; Comité National d’Éthique pour la Santé et les Sciences de la vie (CNESS), Mali n°127/MSDS-CNESS; Comité National d’Ethique pour la Recherche en Santé (CNERS) Niger n°67/2020/CNERS; Inserm IEEC n°20–720; WHO-ERC n° ERC.0003364). all ethical approval and NICE were attached in the Study protocol proof section in the submission system. This study has been retrospectively registered by the Pan African Clinical Trials Registry on June 15th 2022 under the following Trial registration number: PACTR202206525204526.

All individual interviews will be conducted after explaining the relevance of the research and asking for the free and written informed consent of the interviewees. The original consent form will be kept by the site’ Principal Investigator (PI) and NGO in a secure location inaccessible to others, even when moving, throughout the study period and up to 15 years after the end of the study.

Parents or guardians shall be informed of their right, during or after the research, to receive information concerning the health of their child held by the investigator or, where applicable, by the qualified person representing the investigator. If the child is in an emergency situation, the consent process will not be conducted until the child is stabilized. In all cases, the clinical management of the child will take priority over the research. Any clinically significant anomaly detected in the results of the examination or test will be communicated to the parents/guardians and the doctor chosen by them, unless they object.

Participants will not receive any financial reward for their participation.

All data will remain confidential and will only be accessible to researchers via secure access. All agents involved in the collection and/or management of data will be required to sign a confidentiality agreement. The data will be anonymized after collection and kept for 15 years following the end of the study. A copy of the data will be stored on a virtual platform and protected by a password.

## Discussion

AIRE research protocol will provide useful and original information on the introduction of routine PO use into IMCI consultations at PHC level by addressing several West African specificities compared to other regions of sub-Saharan Africa:Children mortality rates in West Africa are among the highest in sub-Saharan Africa and strongly correlated with indicators of poverty, underlying malnutrition and infectious diseases [58–60]. The disease burden is complex. Fever-related illnesses remain one of the leading causes of death in children under 5, including malaria and pneumonia. Malaria is particularly acute in West Africa [61] with prevalence ranging between 30 and 64%. Sickle cell disease is also widespread and is an invisible and underestimated cause of anemia and a neglected cause of morbidity in children under-5 in West Africa [62, 63]. This adds to the context of malnutrition often coupled with specific nutritional deficiencies (lack of iron [64], folates and other micro-nutrients) and the presence of other parasites (especially helminths) playing an underestimated role in “chronic epidemic anemia” [65], which is an underlying factor associated with almost half of deaths of children under-5 in West Africa. Second, all these comorbidities including hypoxemia are frequently neither identified nor treated contributing synergistically to the fatal worsening of severe cases among children in West Africa.The West African health system is also weak with insufficient health resources, low access to health services and insufficient investment in frontline health care. There is a critical shortage of health workers, particularly at the primary health care level and in poor rural areas. As training programs progress, qualified personnel often leave to work elsewhere [66]. This leads to issues of health equity, where there are currently many underserved children and often inadequate quality of care [66, 67]. Inadequate clinical capacity (i.e. inadequate implementation of IMCI guidelines) to identify severe cases in neonates and children means that children with danger signs or signs not specific and with severe illness (including malaria, pneumonia, and other infectious diseases) are missed or misdiagnosed at PHC level and not referred to hospital [67]. In the context of the COVID-19 pandemic, the West African health system has been further disrupted, with an expected indirect impact on both delivery and demand for routine IMCI care among children under-5 that needs to be better described and understood [68].Finally, the cost of care could impact access to care in West Africa: health care for children under-5 is free for families in Niger and Burkina Faso but not in Mali and Guinea except for malaria, tuberculosis, HIV and malnutrition. However, the user fee abolition policy is currently facing a major obstacle such as the sustainability of financing which impacted the cost of care [69]. As it is standard practice to ask families to pay for care at the point of service, the capacity to pay is a major determinant of access to care, particularly for hospital referral creating major social inequities [70]. Generally, urban versus rural populations, and those with higher socio-economic status (SES) and education are more likely to seek care with health providers than lower SES groups or illiterate population. For example, the 2012 Demographic Health Survey in Mali reported that among children who experienced fever in the 2 weeks preceding the survey, 43% of urban populations sought care from a health provider, versus only 29% in rural areas [71].

The initial AIRE research protocol submitted (V1.3 - 5th March 2020, approved by the four National Ethics Committees) before the COVID-19 pandemic, was built on a quasi-experimental comparative before-after PO introduction study design (with three research components assessing the process, impact, and cost-effectiveness). Unfortunately, because of the COVID-19 pandemic having emerged in March 2020, this protocol was biased and the project delayed. To mitigate this bias, we therefore proposed a revised operational non-comparative research study protocol that was consequently also approved and launched in 2021.

However, several issues were discussed during the AIRE study design development that will not be fully addressed:When is the best time to introduce the PO into the IMCI process?

The initial ideas were to introduce PO measurement at the entrance to the IMCI consultation for operational ease, rather than afterwards. The reasons for using PO after examination and classification of the child have been suggested by the International Advisory Group (IAG) as follows: a) the risk of having false positive hypoxemia (1 to 5% of the measurements according to an unpublished data) and therefore sending the child in the hospital without real need, and leading to a risk of overloading the health system if too many children are sent to the hospital, b) other adverse effects potentials for “overuse” of PO, mainly transmission of dirty hands disease between children if PO is not well disinfected; c) the risk that health workers will use SpO2 measurements to classify children without examining them; (d) the risk of overuse of the PO and of having to replace faulty devices more frequently. Thus, the introduction of the PO was systematically integrated after the IMCI consultation in our approved protocol without a comparison group at the time of entry. But the interviews of the HCW will better explore the ideal time to use the PO.2.What SpO2 threshold should be used for hospital referral?

The choice of SpO2 threshold is critical but not obvious, as clinical signs may be difficult to identify at PHC level and may not be reliable predictors of hypoxemia. The 2014 WHO IMCI guidelines recommend providing oxygen therapy when SpO2 is less than 90%. However, this threshold will likely result in misclassification of some children, as cases with non-severe pneumonia when SpO2 ≥ 90% and who have undiagnosed comorbidities will be at high risk of death [72]. Although the quality of the evidence is very low, the WHO, based on hospital evidence [54], strongly recommended in 2016 that children with other emergency signs, with or without respiratory distress, receive oxygen therapy if their SpO2 is < 94%. At the PHC level, the field effectiveness of the SpO2 threshold is unknown; oxygen therapy is not available, and it is probably necessary to choose a more sensitive threshold to anticipate the delay before any actual transfer to the hospital where the oxygen will be delivered. In terms of implementation considerations, the recommendation to give oxygen to all children with emergency signs if SpO2 < 94% must also be weighed against the increased demand that would be placed on resources in the LMIC where oxygen supplies may be scarce [24]. Answering such a question would have required a comparative parallel study design comparing two different SpO2 thresholds strategies (90 and 93%). This study design was unfortunately not retained for ethical and logistical reasons. Additionally, since we will not be tracking moderate IMCI cases in the AIRE protocol, we will also not be able to assess their risk of misclassification.3.How to deal with the situation of care and hospital referral?

The AIRE project will ensure that essential drugs are effectively provided and operational from the start of the project under the country ministries of health auspices: PHC will be equipped with medical equipment for IMCI consultations, antibiotics, ACTs and medical consumables to provide first aid before referral hospital. But increasing the detection of hypoxemia at the PHC level in West African settings raises the question of how to improve emergency oxygen availability or oxygen availability at the peripheral health level. Medical oxygen, which can save lives, is also in short supply in West Africa, especially in small hospitals with poor infrastructure and low human resource capacity. Access to hospital and the administration of oxygen to children who need it is an ethical duty and key elements when considering the implementation of PO at PHC level. This could have an impact both on the use of PO by HCW, and on the effectiveness on child health outcomes. As a result, pediatric unit and pediatric emergency rooms were equipped with injectable antibiotics, ACTs, other drugs, PO, and oxygen concentrators for the treatment of hypoxemia, aspirators and nebulizers at the hospital level. The management of hospital referral of severe cases from all PHC has raised problems in real life conditions: in fact, hospital referral brings a lot of social inequalities in access to health care because often at the family charge with high risk of catastrophic health expenditure in West Africa [73]. There is also an ethical duty to actually take charge of the severe cases that will be identified at the PHC level with the help of PO. This will also have a positive impact on the acceptability of health workers to systematically use PO beyond the end of the project. To address this dilemma, AIRE project suggested to identify actively and support existing local strategies from the start of the project, using and strengthening the local district health system to manage hospital referral.

In the end, the absence of a comparative group will not make it possible to assess the cost-effectiveness impact of using PO into IMCI management at PHC. In settings where resources dedicated to healthcare are limited, a cost-effectiveness analysis would provide a useful estimate of the efficiency of this intervention for decision-makers in West African countries. Furthermore, the selection of the PHC (geographically accessible, access to internet…) may have an impact on the generalization of the study’s results. These will be applicable to PHC, which are alike to those included in this study. In addition, the scaling up of the intervention will also require improving the technical capacity of PHC and district hospitals at the country level to achieve the expected impact of the intervention.

Despite these pitfalls, the current AIRE research project uses a comprehensive, context-specific public health research approach (context, process, outcomes) informing primarily about: process implementation, acceptability, pathways of care, patterns of care, short-term health outcomes, and costs of care, comparing type of IMCI (electronic versus paper versions). These data will provide sufficient evidence for national decision-makers to adopt operational changes that can and promote the timely and appropriate use of PO integrated into the IMCI strategy by HCW at the PHC level, and caregivers’ IMCI-seeking behaviors. The evidence generated is expected to result in scaling up beyond West Africa. This will include transition planning support and information; disseminate the results of the project at national and international level to integrate PO. In conclusion, we hope that the AIRE project will help to identify the brakes and levers of action to optimize the scaling up of an effective use of PO during the IMCI consultation at the PHC level in order to improve survival of children under-5 in the long term in West Africa.

